### Data Collection Methods

#### Electroencephalogram

Participants will be seated in an air-conditioned and sound-attenuated room with a built-in Faraday cage. Data will be acquired using the Compumedics Okti 32-channel acquisition module (Victoria, Australia), a high-definition portable EEG amplifier. Participants will be fitted with Okti EEG recording equipment and seated approximately 80 cm from a 21-inch screen with a keyboard placed in front of them. Electrodes will be positioned according to the international 10–20 montage system, covering locations including Fp1, Fpz, Fp2 and AF3, through to O2. Participants will first complete a brief electrooculogram (EOG) calibration task that will later be used for removal of EOG-related artefacts in the data.^25^ For resting-state, participants will be instructed to focus on a grey cross centred on a black background, measuring 10×10 mm, to record with their eyes open followed by eyes closed resting-state EEG for 6 min each.^26^ In both the EOG calibration and the resting-state, continuous electrophysiological data from 0 to 70 Hz will be recorded using the Compumedics CURRY nine digital signal-processing system (Victoria, Australia), referenced to Cz during active recording. Data will be digitised at 256 Hz.

Resting-state EEG data will be post-processed with standardised pipelines.^27^ Following this, aperiodic pink noise activity will be obtained due to its association with ageing and executive function and is hypothesised to reflect underlying neurobiological processes including neural spiking rates and excitatory-inhibitory balance.^28^

#### Transcranial Magnetic Stimulation (TMS)

SICI and LICI will be studied using a paired-pulse technique that employs a conditioning-test design. The test stimulus will be adjusted to evoke a motor-evoked potential (MEP) of 1 mv amplitude in the first dorsal interossei muscle of the right hand.^29^ To measure SICI, the conditioning stimulus (CS) will be adjusted at 90% of the RMT, and multiple interstimulus intervals (ISIs) will be employed. ISIs include 1, 2, 3 and 5 ms for SICI. LICI will be investigated by implementing two supra-threshold stimuli, and the CS will be adjusted at 120% of the rMT. ISIs include 50, 100 and 150 ms.^29^

#### Cognitive and Mood Assessments

All cognitive and mood assessments and their rationale are outlined in online supplemental material 1.

#### Autonomic Outcomes

Skin conductance will be recorded from the same resting-state protocol used for the EEG, using the Compumedics Okti system and UFI Bioderm Model 2701 at 0.5V.^30^ HRV will be measured using the Polar H10 sensor (Massachusetts, USA) through a 6-min eyes closed EEG task. All data will be stored on a Dell Optiplex 755 desktop.

#### Biochemical Outcomes

The biospecimen collection and processing protocol, biochemical outcomes, and analyses plans are outlined in online supplemental material 2.

### Statistical Methods

A data-driven approach will be applied to de-identified data in Stata^TM^ (StataCorp, Texas, USA). Normality checks will be performed for all variables via visual inspection of histograms to determine whether parametric or non-parametric approaches should be used. Two-tailed independent group *t*-tests with equal variances assumed will be used for all continuous variables, and χ^2^ tests will be conducted for categorical variables. Dependent variables taken at baseline and all following timepoints will be analysed for within-subject and between-subject comparisons using generalised linear models with planned simple contrasts for the within-subjects factor of time. To determine the relationship between immunological, bioenergetic and neuroimmune biomarkers and changes in cognition and mood, a logistic regression analysis will be performed.

A possible signal of efficacy will be explored via effect-size estimates of changes in tertiary outcomes (cognition and mood). Effect sizes, means, SDs and CIs will be reported. Normality checks will be performed, and data will be transformed if necessary. Where appropriate, parametric tests will be applied. A generalised linear model with fixed and random effects will be applied for the tertiary outcomes. Variables will include the between-subjects factor of group (active vs sham) and within-subjects factor of time (baseline, endpoint and follow-up). Pearson correlation coefficients (or their non-parametric counterpart) or multivariate regression involving tertiary outcomes will be conducted. All tests will be carried out one-tailed and using an alpha level of 0.05.

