### Sample Size Determination

An exploratory sample size of 60 participants has been chosen to maximise feasibility and recruitment potential and characterise the potential mechanisms of iTBS in this pilot clinical trial. This sample size was calculated using the following calculator for binary sample sizes: https://www.johndcook.com/binary_sample_size.html. The calculator is based on the rule of thumb which assumes significance α=0.05 and type II error β=0.20 (80% power). We are assuming a potential dropout rate of 20% based on previous clinical trial experience,^24^ which requires an additional 12 participants (72 total).

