### Allocation

Double-blinded randomisation will be facilitated using REDCap, allowing for both concealment and randomisation. A randomisation schedule will be automatically generated by REDCap. Participants will be randomly allocated to receive rTMS or sham at a 2:1 ratio using randomly permutated blocks of 6. The trial will be double-blinded, meaning that the participants and investigator will be blinded to treatment allocation.

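### Equal-variance t-tests are fixed for all continuous variables despite 2:1 allocation; any used on post-treatment data would be miscalibrated if the arms differ in spread (minor, cheap to fix)

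*Protocol article*

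**What the plan says.** Three statements in the protocol article bear on this point.

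- **Test.** Statistical Methods plans t-tests introduced as "Two-tailed independent group" and continues "with equal variances assumed will be used for all continuous variables". Chi-squared tests are named alongside for categorical variables.
- **Allocation.** The Allocation section states: "Participants will be randomly allocated to receive rTMS or sham at a 2:1 ratio using randomly permutated blocks of 6".
- **Size.** Sample Size Determination states "An exploratory sample size of 60 participants has been chosen", raised to 72 for dropout.

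The only check that guides the choice of test is a look at histograms for normality, leading to a transformation or a non-parametric test. No check of spread and no unequal-variance alternative is mentioned. The sentence after the t-tests sends variables measured at baseline and later to generalised linear models. The section closes with "All tests will be carried out one-tailed and using an alpha level of 0.05", which conflicts with the two-tailed t-test sentence. That conflict is a separate matter, so both versions are worked through below.

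**The concern.** The pooled t-test weights each arm's variance by its degrees of freedom, so at 2:1 the active arm dominates the pooled estimate. The variance of the mean difference, by contrast, depends most on the smaller arm. With equal arms the two weightings agree. With unequal arms they agree only if the true variances are equal.

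If participants respond differently to active stimulation, post-treatment values and changes will be more variable in the active arm. The pooled standard error is then too large, intervals are too wide and power is lost. If the sham arm were the more variable, the standard error would be too small, p-values too small and intervals too narrow. The histogram check would not detect either case, because normally distributed data with unequal spread pass it.

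The Discussion says that results will inform effect-size estimates for later trials, so the calibration of intervals matters here as well as the tests.

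**Working it through.** **Inputs from the protocol article.** Allocation 2:1; 60 participants; 72 after dropout; alpha 0.05; equal-variance t-test.

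**The plan's own figures.** The plan states no error rate for the t-test, so there is none to reproduce. The base of 60 cannot be reproduced either, because a calculator for binary outcomes is named without the two proportions. The dropout step reproduces as 60 × 1.2 = 72. At 2:1, 60 gives 40:20 and 72 gives 48:24.

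**Assumption.** The documents give no SD for any outcome. Active-to-sham SD ratios from 1:2 to 2:1 are assumed here, with normal data.

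**Step 1: why the standard error is wrong.** Let n₁ = 40 (active) and n₂ = 20 (sham).

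- True variance of the mean difference: V = s₁²/n₁ + s₂²/n₂.
- Expected value used by the pooled test: P = [((n₁−1)s₁² + (n₂−1)s₂²)/(n₁+n₂−2)] × (1/n₁ + 1/n₂).

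Active SD 1.5, sham SD 1:

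- V = 2.25/40 + 1/20 = 0.10625.
- P = [(39 × 2.25 + 19 × 1)/58] × 0.075 = 1.8405 × 0.075 = 0.1380.
- √(P/V) = 1.14, so the standard error is about 14% too large.
- Approximate two-sided level: 2 × [1 − Φ(1.96 × 1.14)] ≈ 2.6%.

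Active SD 1, sham SD 1.5:

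- V = 1/40 + 2.25/20 = 0.1375.
- P = [(39 × 1 + 19 × 2.25)/58] × 0.075 = 1.4095 × 0.075 = 0.1057.
- √(P/V) = 0.877, so the standard error is about 12% too small.
- Approximate two-sided level: 2 × [1 − Φ(1.96 × 0.877)] ≈ 8.6%.

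**Step 2: simulation.** Zero mean difference, 40:20, 400,000 replicates per row, nominal 5%.

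| SD active : sham | Pooled, two-sided | Welch, two-sided | Pooled, one-sided |
|---|---|---|---|
| 1 : 1 | 4.9% | 5.0% | 5.0% |
| 1.25 : 1 | 3.6% | 5.0% | 3.9% |
| 1.5 : 1 | 2.7% | 5.0% | 3.1% |
| 2 : 1 | 1.8% | 5.0% | 2.3% |
| 1 : 1.25 | 6.8% | 5.0% | 6.3% |
| 1 : 1.5 | 8.5% | 5.0% | 7.5% |
| 1 : 2 | 11.2% | 5.0% | 9.1% |

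Step 1 agrees with the rows for a ratio of 1.5. At 48:24 the pooled two-sided levels are almost the same: 3.5%, 2.7% and 1.8% in one direction, 6.8%, 8.5% and 11.1% in the other. At 30:30 the pooled test stays between 5.0% and 5.2% at every ratio, so the error comes from unequal allocation combined with unequal spread.

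**Step 3: power, two-sided, 40:20.**

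- Active SD 1.5, sham SD 1, difference 1.0: pooled 0.782, Welch 0.853.
- Equal SDs, difference 0.8 SD: pooled 0.819, Welch 0.811.

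**The case against.** The strongest reply is that the t-test is probably not the main outcome analysis. It is paired with chi-squared tests, the usual form of a baseline comparison. The next sentence gives variables measured at baseline and later to generalised linear models. Table 1 shows the EEG, TMS, autonomic, biospecimen, cognitive and mood measures taken at all three time points, so they fall under that sentence. The abstract likewise assigns effects across time points to these models. If the t-tests are for baseline only, randomisation makes the true variances equal and the pooled test is sound. This argument stands as a limit on the weight of the point. It does not remove it, because the t-test sentence covers all continuous variables without restriction.

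A reader might infer from the 8% to 11% rates that the plan inflates false positives. The documents do not support that. Those rates need the sham arm to be more variable, and nothing in the text gives a reason to expect it. The plausible mechanism, varied response to active stimulation, makes the test conservative. If stimulation affects no participant at all, post-treatment variances are equal too and the nominal level holds.

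A reader might also infer that the generalised linear models share the fault. The article does not fix equal residual variances there, and such detail is commonly left to an analysis plan.

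Finally, this is an exploratory pilot. At a ratio of 1.25 the distortion is small, and at the one-tailed level it is milder than at the two-tailed level in both directions.

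**Conclusion.** The concern holds in a limited form. The plan names the variance assumption that is least safe under its own allocation ratio, and its only stated check does not address spread. The consequence is confined to t-tests on post-treatment values or changes, and arises only if the arms differ in spread.

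The size is a range resting on assumed SD ratios and normal data. For a two-sided 5% test, the true level is 3.6% down to 1.8% with a more variable active arm, and 6.8% up to about 11% with a more variable sham arm. At the one-tailed 5% level the ranges are 3.9% down to 2.3% and 6.3% up to 9.1%. The first direction is the more plausible, so the main risk is lost power and over-wide intervals, for example power of 0.782 instead of 0.853. The point is minor because the repeated outcomes also go through generalised linear models.

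**What to change.** In Statistical Methods, replace the equal-variance wording for the t-tests with unequal variances (Welch). If the t-tests are meant for baseline characteristics only, say so; the pooled form is then harmless. The change is one option in Stata. When variances are in fact equal it costs about 0.8 percentage points of power (0.819 − 0.811 = 0.008). Where the sham arm is more variable, Welch shows lower power than the pooled test (0.740 against 0.825 at sham SD 1.5, active SD 1, difference 1.0), but the pooled figure is obtained at a true level of 8.5%, so the two are not comparable. No change to the models is requested on this point.

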**Methods and analysis:**

The aim of this 5-week randomised, sham-controlled, double-blinded pilot clinical trial (n=72) is to assess the underlying mechanisms of action of iTBS in females in the late menopause transition and the relationship with cognition and mood. Data will be analysed using Stata^TM^. Normality checks will guide the choice between parametric and non-parametric tests. Generalised linear models will assess within-subject and between-subject effects across timepoints, with additional regression analyses exploring associations between biomarkers, cognition and mood. Effect sizes, CIs and relevant test statistics will be reported, with significance set at p<0.05.

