### Outcomes

All outcomes were assessed at three time points and full details of the outcome measures are outlined in table 1. As this is a pilot clinical trial, primary outcomes are mechanistic and include cortical activity, assessed via electroencephalography (EEG). Paired-pulse TMS will be used to investigate activity within intracortical circuits as a co-primary outcome. Intracortical inhibition will be measured via short-interval intracortical inhibition (SICI) and long-interval intracortical inhibition (LICI).

**Table 1 T1:** Schedule of Activities

Activity	Online Screening	Phone Screening	Baseline	Endpoint	Follow-Up
Inclusion and Exclusion Criteria	X	X			
FSH Pathology		X			
TMS Adult Safety Screen Questionnaire		X			
Telephone Montreal Cognitive Assessment		X			
EEG Measures			X	X	X
TMS Measures			X	X	X
Heart Rate Variability			X	X	X
Skin Conductance			X	X	X
Saliva Collection			X	X	X
Urine Collection			X	X	X
Memory and Cognitive Confidence Scale			X	X	X
Rey Auditory Verbal Learning Test			X	X	X
D-KEFS Verbal Fluency			X	X	X
Symbol Digit Modality Test			X	X	X
Paced Serial Addition Test			X	X	X
Conners Continuous Performance Test-3			X	X	X
Visual Analogue Scale to Evaluate Fatigue Severity			X	X	X
Patient Health Questionnaire-9		X	X	X	X
General Anxiety Disorder-7			X	X	X
Pittsburgh Sleep Quality Index			X	X	X
Menopause-Specific Quality of Life			X	X	X

D-KEFS, Delis-Kaplan Executive Function System; EEG, Electroencephalogram; FSH, Follicle Stimulating Hormone; TMS, Transcranial Magnetic Stimulation.

Secondary outcomes include changes in subjective cognitive complaints and objective changes in verbal memory, verbal learning, verbal fluency, psychomotor processing speed, working memory, and sustained attention and vigilance. The clinical trial will also assess the effects of an rTMS intervention on the psychological symptom profile as secondary outcomes, including depressive mood, anxiety, sleep quality, and quality of life.

Tertiary outcomes include changes in autonomic function, which will be assessed via skin conductance and heart rate variability (HRV). Changes in inflammatory and energetic markers and neuroactive metabolites will be measured via saliva and/or urine analysis.

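### Logistic regression is named for relating biomarkers to changes in cognition and mood, which the same section treats as continuous scores and for which no binary or ordinal outcome is defined

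*Protocol article*

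**What the plan says.** The Statistical Methods section sets the question as "To determine the relationship between immunological, bioenergetic and neuroimmune biomarkers and changes in cognition and mood" and answers it with one named model: "changes in cognition and mood, a logistic regression analysis will be performed". It gives no responder rule, threshold or ordered categories.

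Elsewhere in that section cognition and mood are handled as quantities. The signal of efficacy is to come from effect sizes of change, and "Effect sizes, means, SDs and CIs will be reported". Normality is to be checked, data transformed if needed, and a model with fixed and random effects fitted by group and time. A further sentence reads: "Pearson correlation coefficients (or their non-parametric counterpart) or multivariate regression involving tertiary outcomes will be conducted".

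The Outcomes section describes the cognitive endpoints as changes in test and scale domains: "Secondary outcomes include changes in subjective cognitive complaints and objective changes in verbal memory, verbal learning, verbal fluency". The Abstract promises only "additional regression analyses exploring associations between biomarkers, cognition and mood", without naming the type of regression.

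**The concern.** Logistic regression needs a categorical dependent variable. A change in a test or scale score is not one until it has been cut, and the article describes no cut. The stated method therefore contradicts the way the same section treats the same outcomes. This is a method that the text fixes, not a detail that it leaves out.

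Three things are at stake:

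- **Precision.** Splitting a continuous change into two groups throws information away, in a trial planned on 60 evaluable participants.
- **Interpretation.** An odds ratio from a split depends on where the split is placed, and no clinical threshold is offered to justify one.
- **Choice of method.** The correlation or multivariate regression sentence could be read as covering the same question. Two competing association methods would then stand side by side with no rule for choosing between them.

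**Working it through.** **Inputs from the documents.** Evaluable sample: "An exploratory sample size of 60 participants has been chosen to maximise feasibility and recruitment potential". Alpha and power: the sample size section "assumes significance α=0.05 and type II error β=0.20 (80% power"), with sidedness not stated there. The total reproduces as 60 + 0.20 × 60 = 72. The article gives no figure for the logistic analysis or for information loss, so there is no plan figure to reproduce on this point.

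**Assumptions, not in the documents.** Normally distributed change scores; a small effect for the efficiency formula; true correlations of 0.30 to 0.40 for the power illustration; a two-sided test at 0.05.

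**Step 1: information kept by a binary split.** Cut a normal outcome at z = c, with a proportion p below it. The efficiency relative to the continuous analysis is φ(c)² / [p(1 − p)]. At the median, φ(0)² = 1/(2π) = 0.159, and 0.159 / 0.25 = 2/π = 0.637. The effective sample size is 60 × efficiency. The number needed to match 60 analysed continuously is 60 / efficiency.

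| Split | Efficiency | Loss | 60 act like | Needed to match 60 |
|---|---|---|---|---|
| 50/50 | 0.637 | 36% | 38 | 94 |
| 30/70 | 0.576 | 42% | 35 | 104 |
| 20/80 | 0.490 | 51% | 29 | 123 |
| 10/90 | 0.342 | 66% | 21 | 175 |

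The median split is the best case for two categories, so the 36% is a floor under these assumptions.

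**Step 2: power at n = 60.** The analytic approximation for the linear analysis is Φ(atanh(r) × √(60 − 3) − 1.96). At r = 0.35 this is Φ(0.365 × 7.55 − 1.96) = 0.79; at r = 0.30 it is 0.65. Simulation from a bivariate normal distribution, rounded, gives:

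| Assumed r | Linear | Median-split logistic, Wald to likelihood ratio |
|---|---|---|
| 0.30 | 65–67% | 43–49% |
| 0.35 | about 80% | 58–63% |
| 0.40 | 90% | 70–73% |

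The range in the last column mainly reflects the choice of test. At r = 0.35, likelihood-ratio power falls further to 58% at a 30/70 split and 51% at 20/80. Statistical Methods also ends by making all tests one-tailed, although it earlier specifies two-tailed t-tests. One-tailed at r = 0.35, power is 88% for linear against 71–73% for median-split logistic, so the gap narrows but remains.

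**Step 3: why the repair should carry treatment arm.** Take 40 active and 20 sham participants (the 2:1 ratio in Allocation), with no relationship within arm and an assumed equal treatment shift in biomarker and score. For a shift of 0.8 SD, false-positive rates are 16% for unadjusted linear, 13% for unadjusted logistic and 6% for arm-adjusted linear. For 0.5 SD there is little inflation (7%, 6% and 5%). A move to linear regression alone would not deal with this.

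**The case against.** The other side has real points, and several stronger readings should not be drawn.

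- **That the analysis cannot be run without losing about a third of the information.** The text does not say binary. An ordinal logistic model would lose only about 5% (efficiency 3/π = 0.955, taken from the Wilcoxon test). The 36% applies to a binary split, and there it is a minimum, not an estimate of this trial's loss.
- **That the cut-point will be picked after the data are seen.** Nothing in the article says when a cut would be set. The article defers the assessments and the biochemical analysis plans to supplements not shown, and a definition could sit there or in a separate analysis plan.
- **That the model omits treatment arm.** The sentence is a one-line summary, not a model formula, and covariate lists are commonly left to a fuller document. Its silence is not an error.
- **That this analysis carries the trial's objective.** The primary mechanistic outcomes are EEG and paired-pulse TMS. The logistic sentence covers only the biomarkers, which the Outcomes section classes as tertiary.
- **That no continuous analysis is planned.** Correlations or multivariate regression are planned, and the Abstract's wording is compatible with linear regression.

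The last point softens the problem but does not remove it. The correlation sentence is not tied to the biomarker question, whereas the logistic sentence is. Its scope is also unclear, because Statistical Methods calls cognition and mood tertiary while Outcomes calls them secondary. Even if a supplement supplies a binary cut-point, the loss from dichotomising would remain.

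**Conclusion.** The point holds as a mismatch between a stated method and the outcome it is applied to. If the sentence is carried out as ordinary binary logistic regression, the cost is substantial for a trial of this size: 17 to 22 percentage points of power at an assumed correlation of 0.35, two-sided (80 − 63 and 80 − 58). Those figures rest on normality, on correlations that no part of the article supplies, and on a median split, which is the most favourable cut. They illustrate the cost and do not predict this trial's power.

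Severity is moderate. The analysis is exploratory, in a pilot, and does not touch the primary outcomes, the randomised comparison or safety.

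**What to change.** In Statistical Methods, replace the logistic regression with linear regression of the post-baseline cognition or mood score on biomarker change, adjusted for the baseline score and for treatment arm, and report the slope with its 95% CI. The arm term is a no-cost safeguard against a shared treatment effect appearing as a biomarker association.

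In the same edit, reconcile this with the correlation or multivariate regression sentence: say whether that sentence covers the biomarker question and, if so, which analysis takes precedence.

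If a categorical outcome is truly intended, define it and its cut-point, or its ordered categories, before unblinding and give the reason for the choice.

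The cost is about one sentence of analysis wording, with no change to data collection or sample size.

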## DISCUSSION

This randomised, sham-controlled, double-blinded pilot trial will explore the neurophysiological, cognitive and mood effects of non-invasive brain stimulation during the late menopause transition. Building on prior research, it aims to address the evidence-practice gap in managing cognitive and mood symptoms via non-pharmacological methods.

As the first study of its kind, an exploratory sample size was selected based on previous mechanistic studies stimulating the DLPFC in healthy individuals, as well as rTMS/iTBS pilot trials reporting cognitive improvements in clinical populations (sample sizes typically 10–30). While efficacy conclusions are limited by the pilot design, the sample size allows for subgroup analyses of mechanistic outcomes. Mechanistic changes were prioritised as primary outcomes due to the exploratory nature of the study and the need to assess protocol feasibility for future efficacy trials. Results will also inform effect size estimates for adequately powered future studies.

Findings from this pilot clinical trial have the potential to advance our understanding of the underlying mechanisms that affect cognition and mood in menopause and offer the potential for new non-invasive treatments to mitigate symptoms. The successful implementation of this pilot trial could inform future trials and offer a scalable intervention to improve cognition and mood in females experiencing the late menopause transition.

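### The possible efficacy signal in cognition and mood is to be read from effect sizes, yet 8 to 11 scales at two visits are each tested at 0.05 with no key scale or visit named

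*Protocol article*

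**What the plan says.** The aim for cognition and mood is stated in the second paragraph of Statistical Methods: "A possible signal of efficacy will be explored via effect-size estimates of changes in tertiary outcomes (cognition and mood"). Effect sizes, means, SDs and CIs are to be reported, from a model with group (active, sham) and time (baseline, endpoint, follow-up). The paragraph then closes with "All tests will be carried out one-tailed and using an alpha level of 0.05". The abstract has a matching general statement: "Effect sizes, CIs and relevant test statistics will be reported, with significance set at p<0.05". Neither sentence sets the cognition and mood outcomes apart as exploratory.

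The Outcomes section describes the family: "Secondary outcomes include changes in subjective cognitive complaints and objective changes in verbal memory, verbal learning, verbal fluency, psychomotor processing speed", followed by working memory and attention, then depressive mood, anxiety, sleep quality and quality of life. It calls these outcomes secondary, whereas Statistical Methods calls cognition and mood tertiary. Table 1 schedules the instruments at baseline, endpoint and follow-up. No instrument or visit is singled out.

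On later use, the Discussion says: "Results will also inform effect size estimates for adequately powered future studies". It also says that the pilot design limits what can be concluded about efficacy.

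**The concern.** Two ways of reading the cognition and mood results are stated together. One is descriptive: estimates with CIs, from which a possible signal may be seen. The other is a significance test of every outcome at a flat 0.05. With many scales, two visits and no key measure, the second reading leaves it open for any favourable p<0.05 to be presented as the signal, even when iTBS does nothing.

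The stake is the next trial. The Objectives section presents this pilot as preparation for studies with efficacy as the primary outcome. If the scale for such a study were chosen because it gave the largest or a significant result here, its effect size would be too high, and the later trial could be too small or use the wrong endpoint.

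**Working it through.** **Plan's own figure.** The plan states no family-wise error rate for cognition and mood, so there is none to reproduce.

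**Inputs from the document**
- Per-test level: 0.05, one-tailed (last sentence of Statistical Methods). The first paragraph of that section instead has "Two-tailed independent group *t*-tests with equal variances assumed", so both cases are shown.
- Scales (Table 1): 6 cognitive (Memory and Cognitive Confidence Scale, Rey Auditory Verbal Learning Test, D-KEFS Verbal Fluency, Symbol Digit Modality Test, Paced Serial Addition Test, Conners Continuous Performance Test-3) and 2 mood (PHQ-9, GAD-7), which makes 8. Adding the Pittsburgh Sleep Quality Index, Menopause-Specific Quality of Life and the fatigue visual analogue scale makes 11.
- Post-baseline visits: 2 (Day 5 and Week 5). The count therefore runs from 8 tests (8 scales, one test each) to 11 × 2 = 22.
- Completers: 60 (Sample Size Determination) at 2:1 (Allocation), so 40 active and 20 sham.

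**Assumption, not in the document:** the test statistics share a common correlation ρ, taken from 0 to 0.7.

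**Chance of at least one favourable result with no true effect.** For k independent tests at one-tailed 0.05 it is 1 − 0.95^k:
- k = 8: 1 − 0.95^8 = 0.34
- k = 22: 1 − 0.95^22 = 0.68

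For correlated tests it is the probability that the largest of k equicorrelated normal statistics exceeds 1.645 (one-tailed), or 1.96 in the favourable direction (two-tailed):

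| Tests | Sidedness | ρ = 0 | ρ = 0.3 | ρ = 0.5 | ρ = 0.7 |
|---|---|---|---|---|---|
| 8 | one-tailed | 0.34 | 0.27 | 0.22 | 0.17 |
| 11 | one-tailed | 0.43 | 0.33 | 0.26 | 0.19 |
| 22 | one-tailed | 0.68 | 0.47 | 0.35 | 0.25 |
| 22 | two-tailed, favourable only | 0.43 | 0.30 | 0.22 | 0.15 |

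The value for a single pre-named test is 0.05 one-tailed, or 0.025 for the favourable side of a two-tailed test.

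**Size of an estimate picked afterwards.** The standard error of a standardised difference is √(1/40 + 1/20) = 0.274 SD. The expected largest of 22 null statistics is 1.91 at ρ = 0, 1.60 at 0.3, 1.35 at 0.5 and 1.05 at 0.7. Multiplying by 0.274 gives 0.52, 0.44, 0.37 and 0.29 SD. The smallest one-tailed significant difference is 1.645 × 0.274 = 0.45 SD. In simulations with separate between-scale and between-visit correlations, the largest null estimate averaged about 0.60 SD when it was also significant.

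**With one cognitive and one mood measure at one visit.** If both were tested one-tailed at 0.05, the chance of at least one favourable false result would be at most 1 − 0.95² = 0.0975.

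**The case against.** The strongest reply is that this is an exploratory pilot whose primary outcomes are mechanistic. The signal is called possible and is to be explored through effect sizes and CIs. The Discussion limits efficacy conclusions, and non-primary outcomes in a pilot do not ordinarily need family-wise control. A key score, a key visit and the handling of multiplicity are often left to an analysis plan, which is not shown here. Learning which endpoint to carry forward may itself be an aim.

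Much of that stands, and it rules out several stronger readings:
- A reader might infer that one p<0.05 on any scale counts as the signal. No text says so; the plan only leaves it open.
- A reader might infer that the effect size handed to the next trial is inflated. That follows only if the largest or a significant estimate is selected, and nothing says it will be. The Discussion sentence on future effect sizes follows one on mechanistic outcomes and does not name cognition or mood.
- A reader might quote a single narrow figure such as 35-44%. Both ends rest on one assumed correlation of 0.5 and on 22 tests. The 44% is the two-tailed chance of significance in either direction, so it includes results favouring sham; favourable only is 22%.
- The count of 22 is an upper reading. The model has group and time, the planned contrasts are on time, and separate active-versus-sham tests at each visit are not spelled out. Fatigue, sleep and quality of life fall outside a narrow reading of cognition and mood.

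What the reply does not remove is the stated rule. The 0.05 sentence closes the very paragraph that introduces the signal, and the abstract's "significance set at p<0.05" has no exploratory exception. The point therefore rests on what the document fixes, and the lack of a multiplicity adjustment is not the complaint.

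**Conclusion.** The point holds as an inexpensive improvement. The plan describes an effect-size exploration but attaches a flat 0.05 test to each of 8 to 11 scales at two visits, with no key measure.

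Under no effect, at least one favourable one-tailed p<0.05 has a chance of about 17-34% for 8 tests and 25-68% for 22. If the tests are two-tailed, the favourable-only chance for 22 is about 15-43%. The exact value depends on correlations that the document does not give, but every case exceeds the single-test value several-fold.

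The upward bias of about 0.29-0.52 SD applies only to an estimate chosen as the largest of 22 when there is no effect, with 40 v 20 completers and no baseline adjustment. Full reporting with CIs carries no such bias. None of this bears on the co-primary EEG and paired-pulse TMS outcomes.

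**What to change.** In Statistical Methods, before unblinding:
1. Name one cognitive and one mood measure at one visit. Their baseline-adjusted active-minus-sham estimates, with CIs, carry the possible signal and supply any planning value for a later trial.
2. Report all other cognition, mood, sleep, fatigue and quality-of-life comparisons as exploratory estimates with CIs.
3. Exclude this family from the closing sentence on one-tailed tests at 0.05 and from the abstract's p<0.05 statement.

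In the same edit, reconcile the secondary and tertiary labels for these outcomes and the one- and two-tailed statements.

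The cost is a few sentences, with no new data or participants. The downside is that a favourable result on a scale not chosen could be reported only as exploratory.
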